## Abstract

**Background:**

Most patients who undergo abdominal surgery recover bowel movements within a week; however, some suffer prolonged intestinal paralysis or postoperative ileus (POI) leading to complications, such as infection and intestinal adhesions, which can extend hospitalization and increase readmission rates, and consequently increasing healthcare costs. Chinese medicine is effective for accelerating the recovery of gastrointestinal function after abdominal surgery. *Xiangbin* prescription (XBP) is the standard prescription for this purpose in our hospital; however, randomized controlled trials of it have not yet been conducted.

**Methods/design:**

This double-blind, randomized controlled clinical trial aims to recruit patients who have undergone abdominal surgery and experienced postoperative dysmotility to evaluate the efficacy and safety of XBP for preventing POI and accelerating recovery. The research will tackle the common problem of slow recovery of gastrointestinal function after surgery. The participants will be patients who undergo laparoscopic radical resection of rectal carcinoma or laparoscopic panhysterectomy of a benign lesion. Primary outcome measures will be time to first flatus, defecation, normal bowel sounds, and liquid/semi-liquid/general diet. Good Clinical Practice (GCP) standards of efficacy and safety will also be evaluated, along with objective investigation of the mechanism of action of ghrelin.

**Discussion:**

This pivotal trial will be a standardized, scientific, clinical trial designed to evaluate the use of XBP for the recovery of gastrointestinal function after surgery, and it will conform to international standards for clinical trials for the recognition of traditional Chinese medicine.

**Trial registration:**

Chinese Clinical Trial Registry, ID: ChiCTR-TRC-14004156. Registered on 3 January 2014.

**Electronic supplementary material:**

The online version of this article (10.1186/s13063-018-2484-z) contains supplementary material, which is available to authorized users.

## Background

It has been shown that the small intestine recovers more quickly after surgery (0–24 h) than the stomach (24–48 h) and colon (48–72 h) [1]. Postoperative ileus (POI) can occur as a common complication of anesthesia and surgery after various types of abdominal surgery [2]. The neuronal reflex required for gastrointestinal motility can be temporarily inhibited during surgery, causing nausea, vomiting, abdominal distension, and delaying the postoperative time to first flatus and defecation [3]. Numerous clinical research studies have shown that failure to restore adequate bowel function can result in a series of complications, including infection and intestinal adhesion, leading to prolonged hospital stay, and increased costs and readmission rates. The incidence of POI after abdominal surgery is 10–30% [4]. Reliable data demonstrate that the total cost of surgery can double for patients with, compared with those without, POI ($16,612 vs. $8316; *p* < 0.05) [5]. The Chinese herbal medicine *Xiangbin* prescription (XBP) has been proven to accelerate the recovery of bowel function [6]; however, its use lacks compliance with Good Clinical Practice standards. To extend and ensure the appropriate use of traditional Chinese medicine (TCM), rigorous studies are needed to ensure the safe and effective use of Chinese herbal medicines for the improvement of gastrointestinal motility.

XBP is prescribed as standard in our hospital to promote recovery of gastrointestinal function after abdominal surgery. The function of XBP has been determined based on previous clinical practice, which has demonstrated that the prescription can safely and effectively restore gastrointestinal motility after abdominal surgery. We have conducted numerous research studies into gastrointestinal motility in recent years, and we consider that anesthesia and surgery lead to the POI, referred to as the syndromes, *Qi* deficiency and *Qi* stagnation, in Chinese medicine. XBP is a compound of *Panax ginseng* (*Renshen*), *Areca catechu* L. (*Binlang*), *Prunus persica* Batsch (*Taoren*), *Lindera aggregata* Kosterm (*Wuyao*), and *Fructus amomi* (*Sharen*). *P. ginseng* (*Renshen*) is an edible Chinese herb that promotes the production of body fluids and has a tranquilizing effect, and ginseng oligopeptides (GOP), small-molecular oligopeptides isolated from ginseng, have been proven to have anti-fatigue effects [7]. *A. catechu* L. (*Binlang*) has the function in Chinese medicine of promoting the circulation of *Qi*, and there is evidence that, one of its components, arecoline, affects gastrointestinal motility by direct binding to M receptors [8]. *P. persica* Batsch (*Taoren*) has the function in Chinese medicine of improving blood circulation and relaxing the bowels and there is evidence that its extract can lower blood viscosity [9]. *L. aggregata* Kosterm (*Wuyao*) has the function in Chinese medicine of promoting *Qi* circulation to relieve pain and one of its components. Total alkaloids have anti-inflammatory and analgesic effects [10]. *F. amomi* (*Sharen*) has the functions in Chinese medicine of removing dampness to restore the normal function of the stomach, while its water extract has a role in promoting gastrointestinal peristalsis [11].

Here, we describe a protocol for a double-blind, randomized controlled, clinical trial to evaluate the safety and efficacy of the use of XBP to promote gastrointestinal function recovery after abdominal surgery.

## Methods/design

This pivotal study has been designed as a double-blind, randomized controlled, clinical trial. Patients who have undergone laparoscopic radical resection of rectal carcinoma or laparoscopic panhysterectomy for benign lesions, between March 2015 and June 2018 at Guangdong Provincial Hospital of Traditional Chinese Medicine, will be selected and invited to participate. Patients will be randomly assigned to either the XBP group or the placebo group using numbers randomly generated by the webtool http://www.gztcmgcp.com/sjxt/login.asp. The efficacy and safety of XBP for patients who have undergone abdominal surgery will be evaluated by comparing various indices in the two different groups, including: time to first passage of flatus, first defecation, normal bowel sounds, and consumption of a liquid/semi-liquid/general diet. The study aim is to determine whether XBP can improve the speed of restoration of postoperative gastrointestinal motility. The study protocol has been approved by the Ethical Committee of the Second Affiliated Hospital of Guangzhou University of Traditional Chinese Medicine (Guangdong Provincial Hospital of Traditional Chinese Medicine). Written informed consent was obtained from all volunteers, and the study conformed to the ethical principles set forth by the Declaration of Helsinki. The study protocol is registered at the Chinese Clinical Trial Registry (http://www.chictr.org.cn/showproj.aspx?proj=5412).

### Participants

Participants who have undergone laparoscopic radical resection of rectal carcinoma in the Gastrointestinal Surgery Department or laparoscopic panhysterectomy of benign lesions in the Gynecology Department of Guangdong Provincial Hospital of Traditional Chinese Medicine will been recruitment. The inclusion, exclusion, and elimination criteria are listed in Table 1.

**Table 1 Tab1:** Inclusion, exclusion, and elimination criteria

Category	Criteria
Inclusion criteria	Patients who have undergone surgery for gastric or colorectal cancer, or hysterectomy for hysteromyoma Age 40–75 years old Duration of surgery, 1–4 h Time under anesthesia, 1.5–4.5 h TCM syndrome, Qi deficiency and Qi stagnation Provision of signed, informed consent
Exclusion criteria	Advanced malignant tumor cachexia, extreme weakness Malignant tumors requiring extended radical surgery Cardiovascular, liver, kidney, brain, or lung co-morbidity, or other serious diseases Poorly controlled hypertension or diabetes Mental disability Allergy to the intervention Pregnant or breast-feeding women Severe malnutrition (serum albumin < 21 g/L, pre-albumin < 0.1 g/L) Repeated abdominal surgery and severe intestinal adhesions Blood loss > 400 mL during surgery Serious complications occurring within 6 h after surgery (e.g., multiple organ dysfunction) Postoperative intraperitoneal hyperthermic perfusion Emergency surgery Prokinetic drugs prescribed after surgery Patient participating in another clinical study, or having participated in another clinical study in the previous month Patient considered inappropriate to participate the study by clinical investigators
Elimination criteria	Do not meet the inclusion criteria, but mistakenly included Worsening condition that cannot be controlled in 3 days Other complications because of interventions, including severe allergy or serious adverse events Serious complications, infection, or requiring a second operation during treatment Refusal to continue the treatment, regardless of the reason

*TCM* traditional Chinese medicine

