### Data collection and statistical analysis

Data will be collected from participants via daily face-to-face and telephone interviews and recorded in the CRFThe statistical package, Epidata 3.1, will be used for data entry. Two people will perform data entry independently, and they will be trained in advance and pass a test before they begin the work. The data will then be transferred to Statistical Package for the Social Sciences (SPSS) software for data analysisThe statistical analyses were pre-specified and performed on an intention-to-treat (ITT) basis. The ITT analysis will include all patients who were randomly recruited, and the per-protocol (PP) analysis includes patients who completed the study and did not have major protocol violations. All analyses are based on the ITT population, and the result of the ITT analysis is compared with the PP analysis to assess the sensitivity. All missing data are analyzed using the last observation carried forward (LOCF) imputation method. Changes from baseline in outcome measurement among the two groups are analyzed using analysis of variance (ANOVA) or the Kruskal-Wallis test when appropriate. The Bonferroni methods for multi-comparisons are performed if the tests are statistically significant. Safety analysis is analyzed mainly using descriptive statistics. All statistical tests are in a two-tailed t test at a 5% level of significance (Additional file 1).Data will be analyzed by an independent statistician. Data for continuous variables are reported using mean (standard deviation; SD) for normally distributed data or median (range) for skewed data. Data for categorical variables are expressed as number (percentage). Intergroup differences are assessed for significance using Student’s *t* test for normally distributed continuous variables or the Mann-Whitney U test for skewed continuous variables. Intergroup differences in categorical data are assessed using the *χ*^2^ test or Fisher’s exact tests (two-tailed), as appropriate. Length of hospital stay is calculated using Kaplan-Meier analysis to compare differences between groups. Data are analyzed using SPSS 19.0 (IBM, Armonk, NY, USA), with the threshold of significance defined as a two-tailed *p* < 0.05.

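### Table 1's elimination criteria act on events after randomization and are not reconciled with the all-randomized ITT analysis

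*Protocol article*

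**What the plan says.** Table 1 (Protocol article, Participants) sets elimination criteria beside the inclusion and exclusion criteria. There are five:

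- "Do not meet the inclusion criteria, but mistakenly included"
- two consecutive items, which the text runs together: "Worsening condition that cannot be controlled in 3 days Other complications because of interventions, including severe allergy or serious adverse events"
- a fourth item, on what may happen while the patient is on study medicine: "Serious complications, infection, or requiring a second operation during treatment"
- a fifth item, on patients who no longer wish to take part: "Refusal to continue the treatment, regardless of the reason"

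Separately, the exclusion list contains "Prokinetic drugs prescribed after surgery", with no time limit attached.

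The section Data collection and statistical analysis defines two sets. For the first, "The ITT analysis will include all patients who were randomly recruited". For the second, "the per-protocol (PP) analysis includes patients who completed the study and did not have major protocol violations". Their roles are fixed as well: "All analyses are based on the ITT population, and the result of the ITT analysis is compared with the PP analysis to assess the sensitivity". The same section handles every missing value by LOCF.

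The primary outcomes (Outcome measures) are all times to a first event: flatus, defecation, bowel sounds and stages of diet. Trial procedure has subjects assessed at least three times a day until discharge, with telephone calls on days 14 and 60.

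**The concern.** Four of the five elimination items describe things that happen once a patient is in the trial: deterioration, harm from the intervention, complications, refusal. They are linked to how well the patient is recovering or to what the treatment does. The Background itself names infection as a consequence of failed bowel recovery, and infection during treatment is one of the items. A patient can therefore meet an elimination criterion because of the condition under study.

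The article does not say what elimination does to the patient's follow-up or data, and the ITT statement does not mention it. If site staff take it as the end of participation, the randomized comparison is left with patients who had no such event. The two arms need not lose the same number or the same kind of patient. The primary efficacy comparison of a trial that calls itself pivotal would then depend on an undefined word.

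**Working it through.** **1. What elimination can mean.** Three readings are possible.

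- *Stopping the study medicine only.* This fits deterioration and complications. It fits poorly with refusal, where the patient has already stopped, and with mistaken inclusion, which is not a reason arising from treatment.
- *Leaving the per-protocol set only.* This is compatible with the text. However, that set is defined by completion and absence of major violations, without reference to the elimination list, and an infection or a re-operation is not in itself a violation.
- *Leaving the trial or the analysis.* This is the most natural sense of the word for refusal and mistaken inclusion. It is also the reading that does not sit with an ITT set of all randomized patients.

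**2. What follows for the primary outcomes.** If patients leave the trial or the analysis, selection is on outcome. If they stay in ITT but assessment stops before the event, LOCF must fill in a time to first flatus, defecation and so on. Before the event there is no earlier value of that time to carry forward. Using the time last seen would count a patient who had not recovered as recovered at that moment.

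**3. The plan's own figures.** From Sample size estimation: 22.06 h and 26.78 h to first flatus, 89 per group, 15% dropout, 105 per group.

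- Difference: 26.78 − 22.06 = 4.72 h.
- Dropout: 89 / (1 − 0.15) = 104.7, rounded up to 105. Reproduced.
- Allowance for losses: 105 − 89 = 16 per group.

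The article gives no SD or power, so the SD is back-solved with two-sided alpha 0.05:

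SD = 4.72 × √(89/2) / (z₀.₉₇₅ + z_power)

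- 80% power (assumed): 4.72 × 6.671 / (1.960 + 0.842) = 11.24 h.
- 90% power (assumed): 4.72 × 6.671 / (1.960 + 1.282) = 9.71 h.

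**4. Illustration of removal.** Assume normally distributed times, no true effect, and elimination of exactly the slowest fraction f of an arm. The mean of those who remain falls by SD × φ(z₁₋f) / (1 − f).

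| Slowest fraction removed | Fall, SD 9.7 h | Fall, SD 11.2 h |
|---|---|---|
| 5% | 1.05 h | 1.22 h |
| 10% | 1.89 h | 2.18 h |
| 15% | 2.66 h | 3.07 h |

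Spurious difference for unequal removal:

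| Arm A / arm B | SD 9.7 h | SD 11.2 h |
|---|---|---|
| 10% / 5% | 0.84 h | 0.97 h |
| 15% / 10% | 0.77 h | 0.89 h |
| 15% / 5% | 1.61 h | 1.86 h |

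The last row is 1.61/4.72 = 34% to 1.86/4.72 = 39% of the planned effect. The difference favours whichever arm loses more slow patients, so it can run either way.

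**The case against.** The strongest reply is that the statistical section already settles the matter: ITT holds all randomized patients, every analysis rests on it, and PP is only a comparison. Table 1 nowhere says that an eliminated patient leaves an analysis set. The article also condenses a fuller protocol that may define the term. Much of this stands. A reader might infer that the two sections flatly contradict each other, but because elimination is undefined, that is not shown.

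A reader might also infer that the list hides adverse effects, since serious adverse events from the intervention are on it. The documents do not support this. Safety assessment provides for recording adverse events at any time in treatment or follow-up, and Trial procedure adds the two calls. An event that triggers elimination has already been seen. All that remains is that the article does not say eliminated patients stay in follow-up and in the safety analysis.

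Loss of assessment is likewise a supposition, because the schedule to discharge carries no condition of staying on treatment. The prokinetic item stands among the exclusion criteria, and its use to remove patients after randomization is only an inference from its missing time limit. The 15% allowance does not decide the matter either, since a plan may inflate for dropout and still analyse by ITT.

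The reply does not dispose of the point. The article itself states outcome-related elimination, all-randomized ITT and LOCF for all missing data. Nothing in it tells site staff to keep assessing eliminated patients, and if assessment stops, the LOCF rule gives no usable value.

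**Conclusion.** The point holds as a failure to reconcile. The elimination criteria depend on events after randomization that are related to outcome or treatment, and the article does not say how they relate to its ITT analysis. Removal from the trial or analysis would select on outcome. Retention without assessment would leave LOCF to supply times that have no meaning.

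The size cannot be read from the documents, which give no elimination rates. The figure of 1.6 to 1.9 h against 4.72 h is an illustration. It rests on a back-solved SD of 9.7 to 11.2 h, normal times, 15% against 5% elimination, and removal of exactly the slowest patients. It arises only if those patients are left out, which the article does not state. Smaller imbalances give under 1 h. Whether the clinical criteria themselves are suitable is not judged here.

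**What to change.** Without changing any clinical stopping rule, state in Table 1 and in the statistical section that:

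- the elimination list governs only discontinuation of study medicine and membership of the per-protocol set;
- patients who meet it continue the scheduled assessments to discharge and the day 14 and day 60 calls;
- they remain in the ITT and safety analyses;
- patients with no observed event are censored in a time-to-event analysis of the primary outcomes, in place of LOCF;
- the prokinetic exclusion applies up to randomization, and later use is recorded and does not remove the patient from ITT.

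Continued assessment matters most, because censoring at the moment of elimination would itself be related to prognosis.

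The cost is a small amendment and some patients with incomplete data in ITT. The assessments and calls are already scheduled. The larger element is the analysis: continuous outcomes are now compared by t test or Mann-Whitney and Kaplan-Meier is planned only for length of stay, so the time-to-event method has to be extended to the primary outcomes.

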### Trial procedure

The entire trial will include a preoperative assessment, an intervention phase (generally 1–7 days), and a 2-month follow-up phase. Included subjects will be randomized to groups receiving XBP or a placebo, using a stratified random system, and acquire a random number (corresponding to numbered drugs) in this phase. Participants will be instructed to take the medicine twice every day after surgery (excluding the surgery day) at 09:00 and 16:00 until defecation occurs. Any remaining medicine will be recovered and recorded. Subjects will be evaluated at least three times per day (between 01:00 and 09:00, 09:00 and 17:00, and 17:00 and 01:00) and the results recorded in a Case Report Form (CRF) until they leave the hospital. The participant flowchart is shown in Fig. 1 and the Standard Protocol Items: Recommendations for Interventional Trials (SPIRIT) Figure for the trial is shown in Fig. 2. Adverse events will be monitored by telephone calls to subjects on the 14th and 60th days after surgery.

**Fig. 1 Fig1:**
[figure not shown]
Participant flowchart

**Fig. 2 Fig2:**
[figure not shown]
Standard Protocol Items: Recommendations for Interventional Trials (SPIRIT) Figure for Xiangbin prescription for the recovery of gastrointestinal function after abdominal surgery (XBPRS) trial

### Intervention

The oral Chinese herbal medicine granule (XBP or placebo) is produced by Guangdong Province Engineering Technology Research Institute of TCM, which holds a Good Manufacturing Practice certificate.

After surgery, all included subjects will be administered conventional therapies, including antibiotics and liquid support. Both groups will receive individually packaged doses of XBP or placebo, with instructions that each dose should be dissolved in warm water and consumed per os twice daily after surgery at 09:00 and 16:00 until defecation occurs.

#### Placebo

The placebo is produced by the same manufacturer as the XBP, and consists of starch with no active ingredients. It is dextrin which matched as closely as possible to the appearance and taste of the XBP. The dose and administration instructions for the XBP and placebo will be identical.

### Randomization

A stratified randomization design will be adopted. Random numbers will be generated by the website http://www.gztcmgcp.com/sjxt/login.asp and saved by professional statisticians.

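### Randomization is stratified but no stated test uses the strata; if the two operations are analysed together and recover at different speeds, the comparisons are conservative and lose some power

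*Protocol article*

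**What the plan says.** The protocol article states the allocation design twice. Under Trial procedure, subjects are randomized "using a stratified random system"; under Randomization, "A stratified randomization design will be adopted". Neither place names the stratification factor.

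The Abstract describes the population as patients having "laparoscopic radical resection of rectal carcinoma or laparoscopic panhysterectomy of a benign lesion". Under Sample size estimation, 89 per group becomes 105 per group after 15% dropout, and 420 participants across the two operations are then to be recruited.

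Data collection and statistical analysis lists the tests:

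- "Changes from baseline in outcome measurement among the two groups are analyzed using analysis of variance (ANOVA) or the Kruskal-Wallis test when appropriate".
- For continuous variables, Student's t "test for normally distributed continuous variables or the Mann-Whitney U test for skewed continuous variables".
- For categorical variables, the chi-square "test or Fisher’s exact tests (two-tailed), as appropriate".
- For length of hospital stay, a Kaplan-Meier comparison between groups.

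The intention-to-treat set is all randomized patients, and all analyses are based on it. No listed test has a stratum term, a stratified version or a comparison by operation.

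**The concern.** Stratified allocation balances the stratum difference between the arms, so that difference no longer adds to the true variability of the treatment contrast. A test that ignores the strata still counts it in the estimated variability. Its standard error is then larger than the true one, the confidence interval is too wide, the actual type I error falls below 5% and power falls.

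Rectal cancer resection and hysterectomy for a benign lesion are different operations, and equal recovery times should not be taken for granted. The planning figures come from gynecologic surgery alone, so the spread behind n = 89 belongs to one kind of surgery; a combined sample would show a larger spread if the two types differ. What is at stake is precision and the chance of detecting the planned 4.72 h difference, not the validity of a positive result.

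**Working it through.** **Reproducing the plan's figures**

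- Dropout: 89 / (1 - 0.15) = 104.7, rounded up to 105, as stated.
- Total: 420 = 4 x 105 = 2 arms x 2 operations x 105. Two groups of 105 would give 210. This is the support for surgery type as the stratum, and it remains an inference.
- The 89 cannot be reproduced forwards, because neither SD nor power is given. Solving n = 2 x SD² x (1.96 + z_power)² / 4.72² for SD at n = 89, two-sided 5%, gives SD = 4.72 x sqrt(89/2) / (1.96 + z_power). That is 11.24 h at an assumed 80% power, or 9.71 h at 90%.

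**Inputs for the check**

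- Difference to detect: 4.72 h in time to first flatus (26.78 - 22.06; Sample size estimation).
- Patients per arm: m = 420 / 2 = 210, the intention-to-treat number, with half in each operation (assumption: equal strata and equal allocation).
- Within-operation SD: s = 11.24 h, assumed equal for both operations.
- Gap D in mean recovery time between operations: not given anywhere, so a range is shown as an assumption.

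**Formulas (normal approximation)**

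- True standard error under stratified allocation: s x sqrt(2/m) = 11.24 x sqrt(2/210) = 1.097 h.
- Standard error that the unstratified test estimates: sqrt(s² + D²/4) x sqrt(2/m).
- Interval width ratio: r = sqrt(s² + D²/4) / s.
- Actual type I error: 2 x [1 - Φ(1.96 r)].
- Power: Φ(4.72/1.097 - 1.96 r) = Φ(4.303 - 1.96 r).

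Worked case, D = 24 h: sqrt(11.24² + 12²) = 16.44 h; r = 16.44 / 11.24 = 1.46; 1.96 r = 2.867; power = Φ(1.436) = 92.4%. With the stratum in the analysis, power = Φ(4.303 - 1.96) = 99.0% whatever D is.

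| Assumed gap D | Interval width ratio | Actual type I error, unstratified | Power, unstratified | Power, stratified |
|---|---|---|---|---|
| 0 h | 1.00 | 5.0% | 99.0% | 99.0% |
| 6 h | 1.03 | 4.3% | 98.8% | 99.0% |
| 12 h | 1.13 | 2.6% | 98.1% | 99.0% |
| 24 h | 1.46 | 0.4% | 92.4% | 99.0% |

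**Sensitivity**

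- With 178 per arm (2 x 89, the evaluable number if 15% drop out), stratified power is 97.7%; unstratified power is 95.9% at 12 h and 86.3% at 24 h. A simulation of 20,000 trials per scenario at this size agreed: 95.8% and 86.0% unstratified, 97.7% stratified.
- With s = 9.71 h (90% power assumed for the 89) and 210 per arm, the width ratio is 1.18 at 12 h and 1.59 at 24 h. Unstratified power is 99.6% and 96.9%, against 99.9% stratified.

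**The case against.** The strongest objection is that the statistical section never says in so many words that the two operations are pooled. Since 420 = 4 x 105, each operation may have been sized as its own two-arm trial, and analysed that way the stated tests lose nothing. The last part is correct, and it is why the loss is stated conditionally. But a separate analysis by operation appears nowhere in the statistical section, which compares two groups in a set of all randomized patients.

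Second, the article condenses a fuller plan, its statistical section cites an additional file that is not shown, and ANOVA could carry a surgery-type factor without a change of method. An adjustment may therefore exist elsewhere. The article does, however, name its tests and call the analyses pre-specified, and as named they do not match the stated allocation. The point rests on that mismatch and not on missing detail.

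Third, the size rests on figures the document does not contain: the SD is back-solved from an unstated power, the gaps have no source, and the factor itself is inferred. All of this stands. A reader might infer a serious loss of power by taking a 36 h gap, which gives 60% with 178 per arm. The document does not support that reading. Such a gap exceeds the whole assumed placebo time of 26.78 h, and the stated analysis set is 210 per arm. At small gaps the loss is negligible.

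**Conclusion.** The point holds as a mismatch between design and analysis: the allocation is stratified and no stated test uses the strata. Its direction depends on no assumed figure. If the strata differ and the operations are analysed together, the tests are conservative; the estimate is not biased and false positives are not inflated.

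The magnitude is conditional on the assumed SD, equal strata and the assumed gap, and may be small: from nothing with no gap to a fall of about 7 percentage points at 24 h (99.0% to 92.4%). If pooled, the trial has more than twice the calculated 89 per arm, which absorbs much of the loss in power but does not correct the interval width. If the true stratification factor is something other than surgery type, the same argument applies to that factor. This is a worthwhile improvement, not a threat to the trial's validity.

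**What to change.** Name the stratification factor under Randomization, and use it in the efficacy comparisons:

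- a surgery-type term in the ANOVA or linear model for continuous outcomes and hormone levels;
- the van Elteren test in place of Mann-Whitney;
- Cochran-Mantel-Haenszel in place of the plain chi-square;
- a stratified log-rank test where times are compared as event times.

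Report the treatment effect by surgery type as supportive. If the two operations are meant to be separate two-arm comparisons of 105 per group, state that instead; the stated tests can then stay as they are on this point.

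The cost is wording only. The type of operation is known for every patient, no extra data or patients are needed, and the article reports recruitment as ongoing, so the change can be fixed before the blind is broken.
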